#### Outcomes

This RCT's primary outcome was virologic control as indicated by an undetectable HIV-1 level on the COBAS® AmpliPrep/COBAS® TaqMan® HIV test kit (Roche Molecular Systems, Inc.), which has a threshold for undetectability = < 20 copies/mL and was conducted at each 3-month assessment visit. The secondary outcome was a behavioral composite of engagement in HIV care scale (75), which integrates current/past ART use, HIV appointments timeline follow back, ART adherence (adherence rating (48) and visual analog scale (49)), and knowledge of current CD4 cell count.

We developed a behavioral composite of engagement in HIV care scale (75) that operationalizes key behavioral dimensions of HIV care engagement: attendance in HIV primary care and ART-related engagement, which includes uptake, adherence, and persistence with ART. Importantly, the composite was designed to measure changes in engagement in response to intervention. For this reason, there is not a separate scale for those on ART vs. not (see Table 3. Behavioral composite of engagement in HIV care scoring). Indicators are additive and, by design, include some overlap. For example, if Participant A tested HIV-positive 2 years ago and has had a primary care visit in the prior 6 months, she would get one point for that indicator. This would also, by definition, give her one point for a primary care visit attended in the prior 12 months (two points total so far). If there were two visits in the prior 12 months that were at least 3 months apart (the current HRSA definition of retention in care), she would get one additional point (three points total so far). If she reports knowing her CD4+ count from a recent test (one point), is taking ART (one point), and her adherence is <80% (no point) but she reports no lapses in ART coverage of > 4 days in the prior 3 months (one point), her total engagement score is six.

**Table 3 T3:** Behavioral composite of engagement in HIV care scoring.

**Engagement indicator**	**Points**
Primary care appt within prior 12 months	+1
Primary care appt within prior 6 months	+1
Continuous care criterion for 12 months	+1
Knows recent (w/in 6 mos) CD4+ cell count	+1
On ART	+1
>80% adherence prior 30 days	+1
>90%adherence prior 30 days	+1
No lapses in ART >4 days in prior 3 months	+1
**Total possible score**	**8**

Another example is Participant B who tested HIV-positive 8 months prior, has never seen a provider for HIV care and thus does not know her CD4+ cell count and is not taking ART. She would score a zero on the index. The goal is to help Participant A increase her ART adherence and for Participant B to link to an HIV primary care provider. If successful, both of these participants would increase their scores on the composite index of engagement by at least one point. Thus, the goal of the intervention is to increase the individual's score on the index of engagement along the HIV care continuum. Favorable score changes on the index of engagement in care is a secondary outcome of this RCT and was hypothesized to be the main driver of improvements in viral suppression (our primary outcome). Using an abbreviated form of the index in one of our available datasets of 253 HIV-infected adults, we found that scores of 4–5 were associated with five-fold increased odds of virologic control and a score of six with a six-fold increase in odds of virologic control, compared to those scoring <4 on the index (see Table 4. Behavioral composite scores and virologic control). The eight-point index allows greater precision to distinguish between levels of engagement in care. We hypothesized that if TWH improve their index scores in response to the *Healthy Divas* intervention, they will increase their likelihood of virologic control.

**Table 4 T4:** Behavioral composite scores and virologic control.

**Index of engagement score**	**% with virologic suppression**	**OR of virologic suppression**
<4 (referent)	15%	—
4–5	47%	5.16^*^
6	55%	6.29^*^

* *indicates a p-value of.05 or less; N = 254*.

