For the secondary outcome of HIV care engagement, we hypothesized that women assigned to *Healthy Divas* will have higher engagement in HIV care at follow-up than those assigned to the control condition as measured by appointment attendance and ART uptake, adherence and persistence (Hypothesis 2). We will use the same GEE methods described above to explore whether TWH in the *Healthy Divas* intervention group have higher HIV treatment engagement relative to those in the control group.

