##### Additional Analyses

To explore the effect of the intervention on hypothesized mechanisms of action, secondary analyses will use GEE to evaluate whether TWH assigned to the intervention report higher post-intervention mean scores on theory-based constructs such as health care empowerment, gender affirmation, adherence self-efficacy, social support, HIV treatment information, and treatment beliefs and expectancies (Hypothesis 3). These analyses will also investigate whether these constructs mediate the relationship between intervention group assignment and virologic control. Statistical mediation will be assessed using the causal inference-based approach of Valeri and VanderWeele, which yields optimal estimates of indirect effects in the presence of binary outcomes and moderator-mediator interactions (100). In these analyses mediators will always temporally precede outcomes to uphold temporal ordering assumptions. For instance, mediators at 3 months will be considered for analyses involving virologic control at 9 months and mediators at 9 months will be considered for analyses involving virologic control measured at 12 months.

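### Four of the eight engagement points look back past randomisation, which lowers the sensitivity of the time-averaged Hypothesis 2 contrast and of the engagement mediator

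*Protocol article*

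**What the plan says.** The behavioural composite in the protocol article (Outcomes, Table 3) has eight one-point items. Four have long look-backs: "Primary care appt within prior 12 months", "Primary care appt within prior 6 months", "Continuous care criterion for 12 months" and "Knows recent (w/in 6 mos) CD4+ cell count". The text above the table explains the continuous-care item as "two visits in the prior 12 months that were at least 3 months apart". The other four items use current status, 30 days or 3 months. The same section states that "the composite was designed to measure changes in engagement in response to intervention".

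Assessments fall at months 3, 6, 9 and 12 (Participant Timeline), and the intervention is finished before month 3 (Trial Design). For Hypothesis 2 the plan says "We will use the same GEE methods described above to explore whether TWH" in the intervention arm have higher engagement. Those methods are a time-averaged post-baseline GEE comparison. Its named covariates are standard care quality and the randomisation strata; others may enter if they improve QIC (Statistical Methods, Outcomes).

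Table 2 groups treatment engagement with the mediators, and Sample Size refers to a mediation component of Aim 2. Additional Analyses says "mediators at 3 months will be considered for analyses involving virologic control at 9 months", and pairs 9-month mediators with the 12-month outcome. Nothing shown limits the look-backs to time after randomisation.

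**The concern.** A point already held because of a visit before enrolment cannot be gained through the intervention. At month 3 most of each 12-month window lies before the trial. The continuous-care point is then nearly out of reach from new visits alone, because it needs two visits at least three months apart. A scale meant to register response to the intervention therefore carries pre-trial behaviour into three of the four visits that are averaged, and into both mediator time points.

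The stake is interpretive. A null Hypothesis 2 or mediation result could partly reflect scoring windows rather than an intervention that failed to change attendance.

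**Working it through.** **The plan's own figures.** Sample Size applies the Hypothesis 1 calculation to Hypothesis 2. With 114 per arm, four measurements, power 0.80 and two-sided α = 0.05 (two-sidedness assumed), h = (1.960 + 0.842) × √[(2/114) × (1 + 3ρ)/4]. This gives 0.235, 0.293 and 0.342 at ρ = 0.20, 0.50 and 0.80. Table 5 prints 0.235, 0.293 and 0.344 at P0 = 0.30, so it reproduces. The worked example for Participant A also reproduces: 1+1+1 (visits) + 1 (CD4+) + 1 (on ART) + 0 (adherence) + 1 (no lapse) = 6.

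**Share of each window before randomisation.** For look-back L at month t, the share is max(0, L − t)/L.

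| Items | Month 3 | Month 6 | Month 9 | Month 12 | Mean |
|---|---|---|---|---|---|
| Two 12-month items | 75% | 50% | 25% | 0% | 37.5% |
| Two 6-month items | 50% | 0% | 0% | 0% | 12.5% |

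An assessment 14 days early adds a little (for example 3.8% of a 12-month window at month 12).

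**Effect on the contrast.** The documents give no visit rates, so this part rests on assumptions. The monthly visit probability is 0.10 before the trial and in control, and 0.17 under intervention (scenario A), or 0.15 and 0.25 (scenario B). The effect is immediate and constant, and 400,000 histories per arm were simulated. The outcome is the arm difference summed over the three appointment items. Scoring as defined is compared with the same items cut off at randomisation.

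| | Month 3 | Month 6 | Month 9 | Month 12 |
|---|---|---|---|---|
| A, as defined | 0.25 | 0.44 | 0.54 | 0.64 |
| A, cut off | 0.32 | 0.49 | 0.59 | 0.64 |
| B, as defined | 0.25 | 0.44 | 0.53 | 0.61 |
| B, cut off | 0.39 | 0.55 | 0.63 | 0.61 |

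Time-averaged, A retains 0.467/0.511 = 91% and B retains 0.456/0.543 = 84%. Repeat runs move these by about a point (83% for B in one).

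**Sensitivity to the visit rate.** A separate model had visits arriving at random at 1, 2 or 4 a year before the trial and in control, with an intervention rate ratio of 1.5 or 2. The ratio of as-defined to cut-off effect was:

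| Visits per year | Month 3 | Time-averaged |
|---|---|---|
| 1 | 0.80–0.82 | 0.94–0.95 |
| 2 | 0.66–0.67 | 0.84–0.86 |
| 4 | 0.37–0.38 | 0.57–0.61 |

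**Women eligible through no appointment in the prior 6 months.** With those six months empty, the as-defined and cut-off contrasts agree at every visit (scenario A: about 0.31, 0.49, 0.59 and 0.64 under both). Only a visit 6 to 9 months before entry can still count, and only at month 3. It uses up the 12-month point, but it also lets one new visit earn the continuous-care point, and the two effects cancel.

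**Month 12 against the time average.** Under the correlation model behind Table 5, the standard error of the time average relative to a single visit is √[(1 + 3ρ)/4] = 0.63, 0.79 and 0.92 at ρ = 0.2, 0.5 and 0.8. The as-defined time average is 73–75% of the month-12 effect. Setting √[(1 + 3ρ)/4] equal to 0.73 and 0.75 gives ρ = 0.38 and 0.42. Below about 0.4 the time average is the stronger test for the appointment items; above it, month 12 is.

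**The case against.** The strongest reply is that nothing here is biased between arms. Pre-trial visits are balanced by randomisation, the contrast is valid for the scale as defined, and the 12-month retention criterion is an established definition that the plan adopts deliberately. The outcome is secondary and described as exploratory, baseline score could enter through the QIC rule, and sensitivity analyses may sit in an analysis plan that is not shown. The validity argument stands, so this is a matter of sensitivity only. The point survives because the scale, the visits and the averaged contrast are all stated, and together they work against the stated purpose of registering change. Trial Design also describes the outcome as within-subject improvement, which sits better with a baseline covariate fixed in advance than with one left to QIC.

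A reader might infer four stronger things that the documents do not support.

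- That the time average shows only 73–75% of the true effect. That ratio takes month 12 as the yardstick and so mixes look-back with the time visits need to accrue. Even with windows cut off at randomisation, the time average reaches only 80–89% of month 12.
- That women out of care at entry suffer most. For those with no visit in the prior 6 months the net loss is about nil. In the simulation they can still earn the continuous-care point at month 3 (12% treated against 7% control in A, 22% against 15% in B).
- That the mediation analysis breaks its promised temporal order. A 3-month score precedes a 9-month viral load whatever its look-back; it is only a less sensitive mediator.
- That month 12 should replace the time average. That is a trade-off, as shown above, and it discards early ART and adherence changes.

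**Conclusion.** The concern holds as a loss of sensitivity. The window shares follow directly from Table 3 and the visit schedule. The size of the loss does not: it depends on assumed visit rates and an assumed immediate, constant effect. For the three appointment items, the time average retains about 83–91% in scenarios A and B, and 57–61% at an assumed four visits a year. The CD4+ item was not simulated. No figure for the whole composite can be given, because movement in the other points is unknown; the proportional loss is smaller if they also respond.

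Use of the composite as the 3- and 9-month mediator is inferred from Table 2, Sample Size and Additional Analyses read together; the last of these does not name engagement among its example constructs. The primary outcome is unaffected.

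**What to change.** - Keep the time-averaged GEE for Hypothesis 2, and name the baseline composite score as a prespecified covariate. This removes noise from balanced pre-trial content but does not restore points that were already held.
- Add an analysis that scores appointment attendance only on time since randomisation or since the last assessment, using the visits recorded at the monthly check-ins (Retention). Show it beside the published 8-point score.
- Do not simply truncate the continuous-care item at month 3, where it would be near zero for everyone. A score based on the interval since the last assessment needs a different attendance measure, because two visits three months apart hardly fit in three months.
- Report the month-12 contrast as supportive, since it is the only scheduled visit with all windows after randomisation.
- In mediation, adjust for the baseline score and use the post-randomisation attendance score at month 3.

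The cost is analysis-plan wording and rescoring of data already collected; the article says analyses were only starting. The drawback is that the rescored version departs from the published scale and loses comparability with it, so both should be reported.

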#### Participant Timeline

From the date that we enrolled our first participant to the conclusion of the final participant's 12-month follow-up assessment, this RCT took 47 months to implement. Follow-up assessments, including viral load assays and surveys, occurred for 12 months post-randomization at 3-month intervals (For measures, see Table 2. Outcomes and measures). A 29-day window, defined as 14 days before and 15 days after the due date, was available for participants to complete follow-up assessments (Figure 1 provides a schematic diagram of the schedule of enrolment, intervention, control, and assessments). At the time of this manuscript submission, RCT analyses were starting, and we anticipate all data analyses and dissemination of primary trial results to conclude in 12 months.

#### Sample Size

Our sample size was selected to accommodate a range of 40–60% undetectable viral load at baseline, which we monitored in consultation with our Data Safety Monitoring Board (DSMB) to ensure enrolment of a sample with sufficient variability in viral load. Power analyses were generated using the two-group repeated proportions module in NCSS PASS 12 (76) to compute minimum detectable effect sizes at the proposed *N* and α = 0.05 and power = 0.80 for the primary analysis to evaluate Hypothesis 1 (TWH randomized to *Healthy Divas* will achieve or maintain higher odds of undetectable viral load than TWH assigned to a treatment as usual control condition). The study enrolled 278 participants evenly assigned to the intervention and control groups. Prior to starting implementation, we assumed 20% attrition, so that data from 228 participants would be available for analysis at all time points (i.e., 114 participants per group). We computed the minimum detectable odds ratio (*OR*), proportion difference (*pdiff*), and standardized proportion difference (*h*) for a time-averaged comparison, assuming four post-baseline measurements and assuming a range of virologic control base rates P_0_ and the within-subject correlation ρ was varied between.20 and.80 (see Table 5 for minimum detectable effect size estimates). Minimum detectable effect size estimates for our primary analyses fall between cutoffs of 0.20 and 0.50 for small and medium standardized effect sizes (77), respectively, suggesting that primary analyses have sufficient power to detect small to small-medium effects.

**Table 5 T5:** Within-subject correlations.

	**P**_**0**_ **= 0.30**			**P**_**0**_ **= 0.55**			**P**_**0**_ **= 0.80**		
**ρ**	* **OR** *	* **Pdiff** *	* **h** *	* **OR** *	* **Pdiff** *	* **h** *	* **OR** *	* **Pdiff** *	* **h** *
0.20	1.64	11.2%	0.235	1.61	11.6%	0.234	1.93	8.5%	0.235
0.30	1.71	12.3%	0.257	1.68	12.7%	0.257	2.07	9.2%	0.258
0.40	1.78	13.2%	0.275	1.75	13.6%	0.276	2.21	9.8%	0.277
0.50	1.84	14.1%	0.293	1.81	14.5%	0.294	2.35	10.4%	0.297
0.60	1.91	15.0%	0.311	1.88	15.3%	0.311	2.50	10.9%	0.314
0.70	1.97	15.8%	0.327	1.95	16.1%	0.328	2.65	11.4%	0.332
0.80	2.03	16.6%	0.344	2.01	16.8%	0.343	2.82	11.8%	0.347

Sample size calculations described above to evaluate Hypothesis 1 were also used for Hypothesis 2 (TWH assigned to *Healthy Divas* will have higher engagement in HIV care) and Hypothesis 3 (TWH assigned to *Healthy Divas* will report more favorable scores on theory-based constructs of healthcare empowerment, gender affirmation, adherence self-efficacy, satisfaction with medical care, social support, HIV treatment information, and treatment beliefs and expectancies). For secondary mediation analyses to address the mediation component of Aim 2 (TWH assigned to *Healthy Divas* will have higher engagement in HIV care than the control group, which will lead to higher odds of virologic control), the R function *getn.logistic.bcs* (78) was used to compute the minimum detectable odds ratio for the indirect effect of the intervention on virologic control *via* a mediator for the worst case scenario depicted in Table 5, *P*_0_ = 0.80 and *OR* for the direct effect = 2.82. Assuming α = 0.05, power = 0.80, a minimum *N* = 228 balanced on a binary intervention arm predictor and a high correlation of 0.80 between the mediator and intervention predictor, the minimum detectable *OR* = 2.49, *pdiff* = 10.9%, and *h* = 0.313. Alternative scenarios with lower base rates, smaller direct effects, or lower predictor-mediator correlations would be able to detect smaller mediation effects at the same power.

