#### Retention

Our retention plan, developed by our team, has successfully retained >90% of research cohorts per year, and we conservatively estimated 80% retention for the 12-month period (80, 81). The retention plan included: presence at a central location close to public transit; maintenance of detailed contact information; skilled staff trackers; a reliable monthly check-in program (see below); graduated incentive payments (see Table 6. *Healthy Divas* incentive schedule); and efforts to foster positive attachments to the study.

Each participant was scheduled for brief monthly check-in visits in months in which there was otherwise no scheduled visit. At this visit, which was highly flexible and could occur in person or by phone, we updated contact information, clarified the next study visit date and time, documented 30-day self-reported adherence and any changes in medication regimens, and recorded any provider visits that had occurred in the prior month. Participants were paid a small incentive for this 10-min visit ($10). For this study, each monthly check-in visit had the added benefit of documenting HIV care appointment attendance while the events were still recent, which improved precision of our self-reported retention in care measurement. This timeline follow-back procedure was used in our pilot with positive results. Staff members had previously reported information available to them to facilitate this data collection. For example, an interviewer was able to say, “The last time we spoke was on [date] and at that time you said you had seen Dr. [provider's name here] at [clinic or hospital name] on [date previously provided]. Since that visit with Dr. X, have you attended any appointments?” We also inquired about missed appointments (i.e., scheduled but not attended) during each time period.

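### Sample Size section: Table 5's P0 = 0.55 column holds P0 = 0.50 values, 278 enrolled with 20% attrition does not give 228, and the power claim overstates the small end

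*Protocol article*

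**What the plan says.** All of this is in the protocol article, mainly under Sample Size.

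- Minimum detectable effects were calculated "to compute minimum detectable effect sizes at the proposed" N, with "α = 0.05 and power = 0.80 for the primary analysis". The value of that proposed N is not printed.
- On enrolment: "The study enrolled 278 participants evenly assigned to the intervention and control groups". On the planning assumption, dated before implementation: "we assumed 20% attrition, so that data from 228 participants would be available for analysis at all time points", that is "114 participants per group". The Retention section agrees on the rate: "we conservatively estimated 80% retention for the 12-month period".
- The effect sizes are "for a time-averaged comparison, assuming four post-baseline measurements", with within-subject correlation ρ from 0.20 to 0.80. Table 5 gives OR, Pdiff and h in three columns headed P0 = 0.30, 0.55 and 0.80.
- The text cites 0.20 and 0.50 as the cutoffs for small and medium h, places the detectable effects between them, and ends "suggesting that primary analyses have sufficient power to detect small to small-medium effects".
- Eligibility Criteria anticipates 50% undetectable at baseline.

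**The concern.** Within a row of Table 5, P0 and Pdiff fix both OR and h. In the middle column the printed values contradict each other under the printed heading. The enrolled number, the attrition rate and the analysable number stand together in one paragraph but do not multiply out. The closing sentence speaks of sufficient power for small effects, while no cell of the table reaches the section's own small cutoff.

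These are the article's power figures for the primary comparison. The section applies the same calculation to Hypotheses 2 and 3, and the mediation calculation reuses 228. A reader of a null primary result will turn to them to judge what was ruled out. If small effects are taken to have been adequately powered, a null will look more conclusive than it is.

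**Working it through.** **Inputs.** From Sample Size: α = 0.05, power 0.80, 114 per arm, m = 4 post-baseline measurements, ρ = 0.20 to 0.80, 278 enrolled 1:1 (139 per arm), 20% attrition. Sidedness is not stated. A one-sided test would give h = 0.208 at ρ = 0.20 against the printed 0.234 to 0.235, so two-sided is used.

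**Formulas.** Design factor DE = [1 + (m − 1)ρ]/m, which is 0.40, 0.625 and 0.85 at ρ = 0.2, 0.5 and 0.8.

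n per arm = [1.960·√(2·p̄·q̄) + 0.8416·√(p0q0 + p1q1)]² · DE / (p1 − p0)²

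h = 2·asin√p1 − 2·asin√p0

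**Step 1: reproduce Table 5.** With n = 114 the outer columns come back to rounding.

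| P0, ρ | Printed OR / Pdiff | Solved OR / Pdiff |
|---|---|---|
| 0.30, 0.2 | 1.64 / 11.2% | 1.64 / 11.2% |
| 0.30, 0.8 | 2.03 / 16.6% | 2.03 / 16.6% |
| 0.80, 0.5 | 2.35 / 10.4% | 2.35 / 10.4% |
| 0.80, 0.8 | 2.82 / 11.8% | 2.82 / 11.8% |

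**Step 2: middle column, internal check (needs no power formula).** OR and h recalculated from the printed Pdiff:

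| ρ | Pdiff | Printed OR / h | At P0 = 0.55 | At P0 = 0.50 |
|---|---|---|---|---|
| 0.2 | 11.6% | 1.61 / 0.234 | 1.63 / 0.238 | 1.60 / 0.234 |
| 0.5 | 14.5% | 1.81 / 0.294 | 1.86 / 0.301 | 1.82 / 0.294 |
| 0.8 | 16.8% | 2.01 / 0.343 | 2.08 / 0.351 | 2.01 / 0.343 |

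For the last row, (0.718/0.282)/(0.55/0.45) = 2.08, while 0.668/0.332 = 2.01. The differences of 0.01 in OR at P0 = 0.50 come from the rounding of Pdiff: solving directly at 0.50 with n = 114 gives 1.61, 1.81 and 2.01. All seven rows fit 0.50 and none fits 0.55.

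**Step 3: middle column, sample size check at ρ = 0.8.**
- P0 = 0.50, p1 = 0.668: (1.366 + 0.578)² × 0.85 / 0.168² = 113.8 per arm, in line with 114.
- P0 = 0.55, p1 = 0.718: (1.335 + 0.565)² × 0.85 / 0.168² = 108.7 per arm.

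Across the rows, the printed differences need 113 to 115 per arm at 0.50 and 108 to 111 at 0.55. Under the printed heading their power with 114 per arm would be 81% to 82%.

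**Step 4: true P0 = 0.55 values, 114 per arm, ρ = 0.2 to 0.8.** OR 1.62, 1.69, 1.77, 1.84, 1.91, 1.98, 2.05; Pdiff 11.4, 12.4, 13.3, 14.2, 15.0, 15.7, 16.4%; h 0.235 to 0.343.

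**Step 5: attrition.** 278 × 0.80 = 222.4, about 111 per arm. 228/278 = 82.0%, so 18.0% attrition. 228/0.80 = 285. The gap is 228 − 222.4 = 5.6 participants (2.5% of 228). With 111 per arm, detectable h is about 0.24 to 0.35, the largest OR moves from 2.82 to 2.87, and power at the 114-per-arm detectable effects is about 79%.

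**Step 6: power at h = 0.20.** Power = Φ(0.20·√(n/(2·DE)) − 1.960). With 114 per arm and ρ = 0.2: Φ(0.20 × 11.94 − 1.960) = Φ(0.427) = 67%.

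| n per arm | ρ = 0.2 | ρ = 0.5 | ρ = 0.8 |
|---|---|---|---|
| 111 | 65% | 47% | 37% |
| 114 | 67% | 48% | 37% |
| 139 (all enrolled) | 75% | 56% | 44% |

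80% power at h = 0.20 would need about 157, 245 and 334 per arm.

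**The case against.** A reader might infer from these slips that the planning numbers as a whole are wrong. They are not: two columns reproduce as printed, and the third does so once headed 0.50.

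A reader might also infer that 228 was miscalculated from 278. The article does not say that. It reports 278 as enrolled, dates the attrition assumption before implementation, and refers to a proposed N that it does not print. 228 is exactly 80% of 285. That 285 was the plan is an inference, but so is the view that 278 was. Moreover, 228 is described as the number with data at every time point. The analysis is GEE with multiple imputation, so participants with partial follow-up contribute, and 222 should not simply be declared the analysis set. What stands is that the printed figures do not reconcile and that nothing shows the detectable effects for the number enrolled.

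On the power claim, a reader might infer that the article promises 80% power at h = 0.20. It does not say so. Its statement that the detectable effects lie between 0.20 and 0.50 is true of every cell, and the h values are printed for anyone to read. What stands is narrower: that range does not support sufficient power at the small end, and even full retention of 278 does not supply it.

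The column label also has mixed consequences. Against true 0.55 values, the printed ORs are slightly optimistic (2.01 against 2.05) and the printed differences slightly pessimistic (16.8 against 16.4 points).

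**Conclusion.** The point holds as three corrections to stated figures.

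1. The middle column of Table 5 is wrong as labelled. This is certain, since it follows from the printed values alone. The size is small: OR changes by at most about 0.04 and h hardly at all.
2. 278, 20% and 228 do not reconcile as printed. Whether the planning figure itself was wrong cannot be settled from the article. The size is again small: about 79% power instead of 80%, and a largest OR of 2.87 instead of 2.82.
3. The power conclusion overstates the low end. At h = 0.20, power is 37% to 67% with 114 per arm and 44% to 75% with all 139. This is the correction that most affects how a null result is read.

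The power figures assume a two-sided 0.05 test, four measurements with a common within-subject correlation, and no gain from covariate adjustment. The first two are supported by the reproduction of Table 5. None of this touches the design, the estimand or the primary test.

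**What to change.** - **Table 5.** Either relabel the middle column P0 = 0.50, which changes no figure and matches the 50% anticipated at baseline, or keep 0.55 and replace the values with those in Step 4 (OR 1.62 to 2.05, Pdiff 11.4% to 16.4%, h 0.235 to 0.343). The authors know which was intended.
- **Sample size.** Print the proposed N from which 228 was derived. Add the detectable effects for the 278 enrolled under 20% attrition: about 111 per arm, h about 0.24 to 0.35, largest OR 2.87, about 79% power at the printed effects.
- **Power conclusion.** Replace the closing sentence with a statement that 80% power is available for h of about 0.23 to 0.35, depending on ρ, and not at h = 0.20, where it is about 67%, 48% and 37% at ρ = 0.2, 0.5 and 0.8 with 114 per arm.

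The cost is a text and table edit, with no extra participants and no change to the analysis. The Participant Timeline section says analyses were only starting, so the correction can precede the results.
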